## Abstract

**Background:**

ATDOM is the Catalan home healthcare program at primary care level. Patients in the home care program are usually frail, elderly people with multiple comorbidities. They are often polymedicated, leading to a high risk of drug-related problems (DRPs). Our hypothesis is that the pharmacist-led individualized review of the pharmacotherapeutic plans of ATDOM patients will be effective in improving the quality of treatments by reducing DRPs in terms of indication, adequacy, effectiveness, and safety.

**Methods:**

Aim: To compare the effectiveness of a standardized pharmaceutical intervention for the review and optimization of pharmacological treatments in ATDOM patients with usual management practice.

Design: Pragmatic randomized clinical trial with a comparable control group, with prospective follow-up regarding the intervention on the adequacy of the pharmacological treatment of patients in the ATDOM program.

Setting: Primary care teams in the Camp de Tarragona Primary Care Area, Tarragona, Spain.

Participants: Four hundred and thirty-two ATDOM patients will be recruited, those who are over 65 years old and who are currently undergoing pharmacological treatment.

Measures: Effectiveness of a six-month long intervention in reducing DRPs per patient and polypharmacy. Additionally, in the intervention group we will evaluate the implementation of the proposals for change or improvement made by the responsible physician.

Analysis: The outcomes will be analyzed on an intent-to-treat basis and the analysis units will be the individual patients. Logistic regression and linear regression models will be used to evaluate the effects of the intervention on dichotomous and continuous variables versus the control arm.

Ethics: The protocol was approved by the Research Ethics Committee of the Jordi Gol Primary Care Research Institute (IDIAPJGol), Barcelona, (19/141-P).

**Discussion:**

If the results of the pharmaceutical intervention are favorable, widespread implementation of the program could be possible. It could be extended to all ATDOM patients or outpatients in general. Interdisciplinary teamwork could be strengthened as a result, which would improve the healthcare continuum.

**Trial registration:**

Retrospectively registered. ClinicalTrials.gov Identifier NCT05820945; Registered 21 March, 2023.

## Background

A drug-related problem (DRP) occurs when, in the application and use of drugs, patients experience or are likely to experience problems associated with these drugs [1]. Studies carried out both in and outside Spain show very disparate data on the prevalence of DRPs, with between 3.9% [2] and 59% [3] of patients being affected. This difference in the percentage of DRPs between the different studies could stem from the differing concepts of DRP, in addition to patient typology. The incidence of DRPs is recorded for in-patients [4] and out-patients [5]. This latter group includes those receiving home care. There are a variety of factors which could increase the risk of DRPs in the home care setting: associated illnesses and polymedication (owing to greater life expectancy), sporadic contact with the physician in relation to chronic illnesses which do not require regular check-ups, healthcare via different providers, lack of teamwork by the interdisciplinary team, and scant patient’s information about their treatment [6]. A recent systematic review revealed a high prevalence of DRPs, particularly amongst home-dwelling elderly patients [7]. Certain categories of DRPs, such as adverse reactions to medication or medical interactions, are of considerable clinical significance as they can result in hospitalization [8]. In relation to the importance of DRPs in outpatients, while it is true that the majority of DRPs would not have caused the patient any harm, they could have affected the effectiveness of the treatment [9].

A clinical medication review is a structured process whereby the therapeutic efficacy of each medication is assessed and correlated with the evolution of the pathologies treated. It also studies the prevention and resolution of DRPs, treatment adherence and the understanding the patients have about the pharmacological treatments and their own pathologies. The objective is to decide whether drugs need to be added, withdrawn or continued, and to evaluate the benefits and risks the treatment involves [10]. This is based on the interdisciplinary work of medical professionals, nurses and social workers. The role of pharmaceutical services within the healthcare team must also be considered, with optimal communication between physicians and clinical pharmacists being of particular importance [11]. Intervention led by clinical pharmacists for reviewing medication was able to identify, minimize and resolve DRPs in elderly patients in the primary care services [12] as well as in home care patients [13], especially among the elderly population in home care settings [14].

The Domiciliary Healthcare program (ATDOM), within the Catalan primary care system, organizes care and attends to patients with chronic or acute health problems who have difficulty getting to health centers. The program aims to foster greater autonomy and improve quality of life for patients, and especially to ensure continuity of care, given that it involves the coordination of all healthcare areas [15]. An ATDOM patient's treatment plan is established once the patient and caregiver's needs have been evaluated in terms of such key aspects as communication, coordination, symptom control, continuity of care and treatment support. However, this plan is not proactively reviewed when the patient enters this system or on a periodic basis. Patients such as these, who may be fragile and have multiple morbidities, are more likely to be polymedicated as well.

To optimize medication for polymedicated patients, we can submit these patients' treatment plans to a regular reassessment in order to detect DRPs. In this pharmacotherapy review, the adequacy of the patient's medication plan is assessed and proposals are made with a view to improving the patient's health as well as the economic sustainability of the healthcare system.

This pragmatic study aims to assess the efficacy of the medication review program during the implementation process. Our hypothesis is that the pharmacist-led individualized review of the pharmacotherapeutic plans of ATDOM patients will be effective in improving the quality of treatments by reducing DRPs in terms of indication, adequacy, effectiveness, and safety.

### Methods/design

To design this protocol, the SPIRIT 2013 Statement [16] was addressed. The current version of the protocol is V1, which is registered in ClinicalTrials.gov (ID NCT05820945, first submitted on 21 March, 2023; first posted on 20 April, 2023; see https://www.clinicaltrials.gov/study/NCT05820945 for details). All items from the World Health Organization Trial Registration Data Set are summarized in Table 1.

**Table 1 Tab1:** World health organization trial registration data set

Data category	Information
Primary registry and trial identifying number	ClinicalTrials.gov Identifier NCT05820945
Date of registration in primary registry	20 April, 2023
Secondary identifying numbers	19/141-P
Source(s) of monetary or material support	Jordi Gol Primary Care Research Institute (IDIAPJGol)
Primary sponsor	Fundació d'Investigació en Atenció Primària Jordi Gol i Gurina
Secondary sponsor(s)	Catalan Health Institute
Contact for public queries	CS [[contact]]
Contact for scientific queries	CS, Pharmacy Unit, Camp de Tarragona Primary Care Area, Catalan Health Institute, Tarragona, Spain
Public title	A Pharmaceutical Intervention to Reduce Drug-Related Problems in a Home Healthcare Program
Scientific title	Evaluation of a Pharmacist-Led Intervention to Reduce Drug-Related Problems in Patients Included in a Home Healthcare Program: A Pragmatic Randomized Clinical Trial
Countries of recruitment	Spain
Health condition(s) or problem(s) studied	Polypharmacy Potentially Inappropriate Medications
Intervention(s)	Active comparator: pharmacist-led medication review at patient level, and change proposals at physician level
	Placebo comparator: usual pharmacotherapy management
Key inclusion and exclusion criteria	Inclusion Criteria: patient in the home care program, sixty-five years of age or older, and active pharmacological treatment plan with at least one drug
	Exclusion Criteria: the responsible physician considers that participation may harm the patient
Study type	Interventional
	Allocation: randomized; Intervention model: parallel assignment; Masking: single (outcomes assessor)
Date of first enrolment	2 March, 2020
Target sample size	432 patients
Recruitment status	Recruiting
Primary outcome(s)	Total DRPs, DRPs per patient, and number of patients with one or more DRP (time frame: baseline and 6 months follow-up) Number of associated drugs per patient and number of polymedicated patients (≥ 8 different drugs, time frame: baseline and 6 months follow-up)
Key secondary outcomes	Number of proposals issued by the pharmacist (time frame: baseline and 6 months follow-up) Number of proposals implemented by the physician (time frame: 6 months follow-up)

*DRP *Drug-related problem

### Aim

The aim is to compare the effectiveness of a standardized pharmaceutical intervention for the review and optimization of pharmacological treatments in elderly patients on the ATDOM program with usual management practice.

In particular we want to determine the effectiveness of the program by way of a six-month intervention trial in order to (1) reduce DRPs per patient, and (2) reduce polymedication. In the intervention group, we will evaluate the implementation of proposals for change or improvements made by the physician in charge.

### Design

Pragmatic controlled clinical trial for assessing healthcare intervention with random distribution of patients into two groups: (a) intervention group, in which patients will receive the pharmaceutical intervention being assessed, and (b) the control group, in which the patients' pharmacotherapy plans will be managed according to the usual criteria and procedures. Pharmaceutical intervention forms part of a range of primary care services and its assessment will be carried out under implementation conditions in real healthcare practice. If this pharmaceutical intervention – which is the object of assessment – proves effective, the patients in the control group will receive the same treatment once their participation in the study is over.

### Study setting and patient sample

The study will be carried out at 10 primary care centers within the Camp de Tarragona Regional Health Authority (Catalan Health Institute) in the Tarragona province (Catalonia). Participation in the study by family physicians from these centers will be voluntary.

The patients from the participating physicians will be eligible if they receive care through the ATDOM program, if they are 65 years old or over, and if they have an active pharmacological treatment plan involving at least one drug. It will be up to the responsible physician to decide if there are any reasons why a patient may be excluded, for example, if their participation might cause them harm. Those patients who are taken into care homes or long-term nursing facilities, or who pass away during the period of the study will also be excluded from the analysis.

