### Statistical methods

#### Sample size

Based on a review of the literature [7, 14], as well as an exploratory analysis of 100 patients eligible for the study, we assume that in our target patient population the proportion of patients with at least one DRP will be around 60% and we hope to be able to detect a reduction of ≥ 15% in the intervention group after six months. If we accept an alpha risk of 0.05 and a power of 80% in a bilateral contrast, and assume a 20% loss of patients in the process (patients who go into a care home, or into a long-term nursing facility, or who pass away during the study period), we need to include 216 individuals in each group (Fig. 2).

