### Data analysis

The principal analyses will be carried out by intention to treat, taking the patients in each group according to their initial random assignment, independently from the adherence to the pharmaceutical intervention and the recommendations made. The results will be measured in individual patients, although the intervention will be largely directed to the attending physician in the form of instructions or change recommendations. In the analyses we will bear in mind the potential loss of independence that might occur in observations when patients are treated by the same physician (cluster effect). We will first compare both study groups to check that their baseline characteristics are similar. The principal result variables (dependent) will be the number of DRPs per patient, the proportion of patients with DRPs, the number of drugs per patient and the proportion of polymedicated patients. To assess the effects of the intervention on the dichotomous variables we will use multilevel logistic regression models with mixed effects using an Odds Ratio estimate (IC95%) of the intervention group with respect to the control group as an effect measure. To measure the effect on the continuous variables we will use linear regression models with random effect, estimating the differences in adjusted means (IC95%) for the intervention group versus the control group. The statistical significance will be established as *p* < 0.05. For these calculations, we will use the R statistical package.

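### Randomised patients who die or enter a care home are excluded from the analysis, which conflicts with the stated intention-to-treat analysis and creates a risk of selection bias

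*Protocol article*

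**What the plan says.** The protocol article makes three statements that bear on who is analysed.

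- **Study setting and patient sample.** The exclusion rule begins "Those patients who are taken into care homes or long-term nursing facilities" and ends "or who pass away during the period of the study will also be excluded from the analysis". Its events occur during the study, so after assignment.
- **Data analysis.** "The principal analyses will be carried out by intention to treat, taking the patients in each group according to their initial random assignment", whether or not the intervention and its recommendations were followed. The Abstract agrees: "The outcomes will be analyzed on an intent-to-treat basis".
- **Sample size.** The calculation asks the reader to "assume a 20% loss of patients in the process (patients who go into a care home, or into a long-term nursing facility", with death as the third reason. These are the events in the exclusion rule.

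No section names a modified intention-to-treat set, or a target population of patients alive and at home at six months. The Intervention section states that physicians and patients are not blinded, while the results are measured blind. The Measurements section takes outcomes from the prescription module of the electronic record at baseline and after six months.

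**The concern.** Intention to treat protects the comparison because group membership is fixed before anything happens to the patient. The exclusion rule makes membership of the analysed set depend on what happens during the following six months.

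The protocol itself gives reasons why these events may be related to the outcome. Its Discussion links drug-related problems (DRPs) to morbidity and mortality, and its Background says that some can lead to hospitalisation. The intervention can stop, change or start drugs, so an effect of allocation on death or admission to a facility cannot be ruled out. If the excluded patients differ between arms, in number or in type, the remaining groups are no longer those that randomisation produced. The result would still be published as intention to treat.

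The rule applies to every principal variable: DRPs per patient, the proportion with a DRP, drugs per patient, and the proportion polymedicated. The plan expects it to remove a fifth of the patients.

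**Working it through.** **1. Inputs from the Sample size section.** Proportion with at least one DRP 60%; reduction to be detected 15%; two-sided alpha 0.05; power 80%; loss 20%; 216 per group.

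**2. The plan's own figure.** Read the reduction as absolute, 60% to 45%. The mean proportion is 0.525.

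n = [1.960 × √(2 × 0.525 × 0.475) + 0.842 × √(0.60 × 0.40 + 0.45 × 0.55)]² / 0.15² = 172.8

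172.8 / (1 − 0.20) = 216.0 per group.

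The stated 216 is reproduced (rounding up to 173 before inflating gives 217). A relative reduction of 15%, 60% to 51%, would need 478 per group before loss and 598 after it, so the absolute reading is the one used. The sample size is therefore consistent with the exclusion, and the fault lies in the analysis population.

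**3. Expected exclusions.** 0.20 × 432 = 86.4, about 86 patients or 43 per arm, leaving about 173 per arm. This is a planning figure and not an observed rate.

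**4. Possible bias with no true effect.** Let 60% of all randomised patients in each arm have a DRP. If a fraction d is excluded and a proportion q of those have a DRP, the analysed rate is (0.60 − d × q) / (1 − d). The documents give no exclusion rates by arm, so every d and q by arm below is assumed.

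| Assumed pattern | Intervention | Control | Apparent difference |
|---|---|---|---|
| d = 20%, q = 80% in both arms | 55.0% | 55.0% | 0 |
| d = 25% vs 15%, q = 80% in both arms | 0.40/0.75 = 53.3% | 0.48/0.85 = 56.5% | −3.1 points |
| d = 20% in both arms, q = 80% vs 60% | 0.44/0.80 = 55.0% | 0.48/0.80 = 60.0% | −5.0 points |

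Another form of the last pattern excludes 27% of intervention patients with a DRP and 10% of those without, against 20% of both in control. The intervention rate becomes 0.6 × 0.73 / (0.6 × 0.73 + 0.4 × 0.90) = 0.438/0.798 = 54.9% against 60.0%, a difference of −5.1 points. Overall exclusion is almost the same in the two arms (20.2% and 20%), so equal numbers lost do not rule out bias.

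**5. Power if the exclusion is removed.** This uses the same pooled-variance formula.

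- 173 per arm, 60% vs 45%: z = 0.84, power 80%. This is the lower limit on numbers, with no outcome recovered for anyone now excluded.
- 216 per arm, 60% vs 45%: z = 1.17, power 88%. It needs an outcome for everyone and the full effect in everyone.
- 216 per arm with no effect in the patients now excluded: the effect is 0.80 × 15 = 12 points, 60% vs 48%, z = 0.55, power 71%.

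**The case against.** The Data analysis section spells out intention to treat only by assigned arm and regardless of adherence. It does not say in so many words that every randomised patient has an outcome. The exclusion rule is prespecified, worded alike for both arms, and allowed for in the sample size. A patient who has died has no six-month DRP or drug count, so some loss cannot be avoided. All of this stands, and it limits what can be claimed. It does not remove the conflict: dropping randomised patients for later events is not an analysis of the groups as randomised, and the article names no other population.

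A reader might infer four stronger points that the documents do not support.

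- **That a fifth of the trial is biased, or that the trial will show a false benefit of about 5 points.** The 20% is an allowance for loss. The 5 points depend on an assumed pattern that differs by arm, and the bias is zero when exclusions are alike. Nothing in the article shows that the programme changes death or institutionalisation within six months.
- **That usable data are being thrown away for all these patients.** Outcomes are defined at six months. The article does not say whether the record stays accessible or current after care-home entry.
- **That keeping everyone simply raises power to 88%.** That needs the full effect in all patients; with dilution to 12 points it is 71%.
- **That the last plan before death is the obvious substitute outcome.** It carries an earlier value forward, and an early death may come before the review has acted. Non-adherence counts as a DRP (Table 2) and adherence is assessed after six months, so a shortened window does not measure the same thing. Imputing a six-month outcome after death is also open to dispute.

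The SAP could hold imputation models and sensitivity analyses, and their absence here is no fault. The exclusion is different because it is a rule that the article states.

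**Conclusion.** The point holds as a conflict between stated rules. One section removes randomised patients for death or institutionalisation during the study, and two others call the principal analysis intention to treat. The confidence is high for this conflict, which needs no assumption. About 86 of 432 patients are affected if the protocol's own 20% is right.

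The bias is possible and not demonstrated. Over the patterns tried it ranges from 0 to about 5 points, up to one third of the 15-point target, and its non-zero values rest wholly on assumed differences between arms. Its direction cannot be known in advance. The conflict should be resolved before analysis because it governs every principal variable.

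**What to change.** - Delete the blanket exclusion in the section on study setting and patient sample, and define the principal set as all randomised patients by assigned arm.
- Include patients who enter a care home or nursing facility, using the six-month electronic prescription record where it is accessible.
- State in advance how deaths are handled. Examples are a principal estimate accompanied by a sensitivity analysis that uses the last recorded plan, or a named while-alive estimand. Do not impute a six-month outcome after death by default.
- Report deaths and institutionalisations by arm.
- Keep the analysis of patients still at home at six months as a sensitivity analysis.

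If the sponsor prefers to keep the exclusion, the Abstract and the Data analysis section should stop calling the analysis intention to treat. They should state the population as patients alive and at home at six months.

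The cost is a change of wording and extra record review, with no increase in the 216 per group. The downside is possible dilution of the effect, with the loss of power shown above. The number of outcomes recovered will lie between 173 and 216 per arm, because the protocol does not split the 20% into deaths and moves.

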### Sampling and randomization of patients

The eligible patients will be assigned by a primary care pharmacist either to the intervention group or the control group from the patient lists of each participating physician, following a random procedure using the https://www.random.org/ platform.

### Intervention

The intervention will consist of a primary care pharmacist carrying out a clinical review of the medical records and pharmacological treatment plans established for the patients registered on the ATDOM program. The pharmaceutical review procedures are systematized in the document "Rational Use of Medication. Basic medication management in chronic patients: reconciliation, review, deprescribing and adherence” [17], published by the Catalan Department of Health, part of the Camp de Tarragona Regional Authority’s primary care services portfolio (Catalan Health Institute). The pharmacist will review the instructions for each drug in the treatment plan in terms of the patient's pathologies, how appropriate the medication is for their age and clinical conditions (e.g. kidney failure, liver failure or other comorbidities), the suitability of the dosage, treatment instructions and duration, the effectiveness of the treatment in relation to the intended therapeutic goal, the safety of the medication and adherence to the treatment (Table 2). This review will be based on the Beers 2019 criteria [18], STOPP-START [19], Priscus [20] and EU(7)-PIM list [21]. Adherence to the treatment will be monitored using information about the medicines dispensed from the pharmacy office which is registered on the electronic prescription module.

**Table 2 Tab2:** Classification of drug-related problems (DRPs) that can be detected in a pharmaceutical review

Type	Drug-related problem	Example
**Indication**	Unnecessary medicine	An antiplatelet drug used preventatively in primary care is an unnecessary medicine according to current guidelines
	Medicine not indicated or inappropriate for the condition it is intended to treat	
	Lack of prescription for a necessary medicine	
**Adequacy**	Inappropriate medicine for the patient owing to age, medical situation or underlying pathology	Glibenclamide is an inappropriate medicine in geriatrics as it is a sulfonylurea with a prolonged half-life which can cause serious hypoglycemia
	Dose is higher or lower than the correct/recommended dose	
	Frequency of administration incorrect or not recommended	
	Drug form incorrect or not recommended	
	Treatment is longer or shorter than the correct or recommended period	
	Administration time incorrect or not recommended	
**Effectiveness—efficiency**	Lack of adherence	A drug is not effective for a patient because he/she is not taking it
	Therapeutic goal is not reached	
	Therapeutic goal is reached but the intensity of the pharmacological treatment must be reduced	
	Not the most effective-efficient alternative	
**Safety**	History of allergy or other adverse reaction to the same medication or similar	Metformin is a drug which is not recommended for patients with glomerular filtration of < 30 ml/min/1.73 m^2^)
	Drug with contraindications	
	Therapeutic duplication	
	Drug-drug interaction	
	Drug-food interaction	
	Lack of analytical control	

After the review process, a meeting will be held between the pharmacist and the physician in charge in which the DRPs detected will be discussed (Fig. 1) and a series of recommendations for improvement and proposals for change will be made. The proposals might be: (a) suspending treatment of a drug, (b) changing the medication, (c) changing the dosage, (d) changing of posology, (e) starting a new treatment, (f) monitoring the clinical and/or analytical variables, and (g) interventions to encourage adherence to the treatment. Thereafter, the physician will make a global assessment of the improvement and adaptation treatment plan and in exercising his/her responsibility will decide to what degree and/or which points to adhere to in the plan. In any case, the proposals, their justification, the expected advantages and possible drawbacks will be explained and agreed with the patient and, if necessary, with the caregiver or responsible family member. The whole procedure will be recorded in the patient's clinical record.

